### **11.6 Immunogenicity Assessments**

Antibodies to sonelokimab will be evaluated in serum samples collected from all participants according to the SOA (Section 3, [Table 1](#)). At dosing visits, the samples will be collected prior to dose administration. Details on the collection and shipping of immunogenicity samples are in the Laboratory Manual. These samples will be analyzed by the sponsor's designated laboratory.

The detection and characterization of antibodies to sonelokimab will be performed using a validated assay method by or under the supervision of the sponsor.

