#### **6.1.4 Immunogenicity Analysis Set (IG Analysis Set)**

The IG analysis set is defined as all participants who received at least one dose of sonelokimab and who have at least 1 sample obtained for the detection of antibodies to sonelokimab.

In the IG analyses, participants will be analyzed according to the treatment they actually received, regardless of the treatment they are randomized to.

The IG analysis set will be used for all immunogenicity analyses related to the Part A and A+B.

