### 8.7.1 Immunological Analyses

Antibodies to sonelokimab will be evaluated in serum samples collected for Arms 1, 2, & 3 (120 mg Q2W, 60 mg Q2W and 60 mg Q4W sonelokimab) at Baseline, Week 2, Week 4, Week 8, Week 12, Week 14, Week 16, Week 20, Week 24 and the safety follow-up visit. At dosing visits, the samples will be collected prior to dose administration.

Up to three separate ADA types may be assessed: ADAs that bind to sonelokimab ('ADA'); ADA to a modified version of sonelokimab ('mADA') and ADA that neutralise the activity of sonelokimab ('NAb ADA'). Results for mADA will only be available for ADA baseline positive participants. NAb ADA results will only be available for the ADA positive samples.

Summary tables for each ADA type will be prepared to record where applicable the number and percentage of participants who are:

- ADA positive at baseline;
- ADA positive at any visit post-baseline;
- ADA positive at baseline and any visit post-baseline;
- ADA positive post-baseline but not at baseline;
- Treatment-emergent ADA defined as either:
  - ADA positive post-baseline but not at baseline, or
  - Treatment boosted: > 4-fold increase in ADA titers at any post-baseline timepoint compared to baseline, if ADA positive at baseline. [ $10^{(\text{post-baseline log10 titer} - \text{baseline log10 titer})} > 4$ ]
- persistent positive (positive at more than one post-baseline visit where the first and last ADA-positive visits are separated by a period of 12 weeks or longer; or positive at last post-baseline assessment and not at baseline; or positive at a visit with less than 12 weeks before an ADA-negative last visit);
- transient positive (positive at only 1 post-baseline visit and not at baseline; or positive at two or more visits where the first and last ADA-positive visits are separated by a period less than 16 weeks and the last visit is negative).

The log10 titer values for the ADA and mADA (not NAb ADA) will be summarised by visit and treatment arm.

Additional analyses may be performed at the sponsor's discretion but they are beyond the scope of this SAP and will be specified in a separate document, if needed.

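### SAP 8.7.1 defines persistent and transient ADA so that they overlap, with no precedence rule, and its Arms 1–3 sentence conflicts with the immunogenicity analysis set

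*Combined protocol and SAP*

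**What the plan says.** **Persistent (SAP 8.7.1)** has three alternative clauses:

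- P1: "positive at more than one post-baseline visit where the first and last ADA-positive visits are separated by a period of 12 weeks or longer"
- P2: "positive at last post-baseline assessment and not at baseline"
- P3: "positive at a visit with less than 12 weeks before an ADA-negative last visit"

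**Transient (SAP 8.7.1)** has two:

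- T1: one positive post-baseline visit in a baseline-negative patient. There is no condition on the last visit.
- T2: "positive at two or more visits where the first and last ADA-positive visits are separated by a period less than 16 weeks", with a negative last visit.

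The section gives no order of precedence and does not say that the categories are exclusive.

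**Who is evaluated.** SAP 8.7.1 opens with "Antibodies to sonelokimab will be evaluated in serum samples collected for Arms 1, 2, & 3". SAP 6.1.4 is not limited by arm: "The IG analysis set is defined as all participants who received at least one dose of sonelokimab", with at least one ADA sample. It assigns that set to all immunogenicity analyses for Part A and Part A+B, and SAP 8.7 says that the set will be used. SAP 7.1 places the ADA baseline at the last sample before the first sonelokimab dose. Protocol 11.6 says: "Antibodies to sonelokimab will be evaluated in serum samples collected from all participants".

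**The concern.** Immunogenicity is part of a stated secondary objective, and ADA is a named endpoint. Readers normally take persistent and transient as a partition of the ADA-positive patients. As written, one patient can fall in both rows, so the two percentages can add to more than the ADA-positive total. A programmer who notices must choose a precedence rule that the SAP does not give, and the choice moves patients between rows.

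The Arms 1–3 sentence is a second, separate point. Placebo participants who enter Part B and adalimumab non-responders start sonelokimab there (SAP 3.3.1). They belong to the analysis set but not to the arms that 8.7.1 names, so two programmers could produce different tables from the same SAP.

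**Working it through.** The SAP states no figure to reproduce. The check applies the five clauses literally to every pattern of positive and negative visits with at least one post-baseline positive.

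**Inputs**

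- Non-US visits (SAP 8.7.1; follow-up at nominal Week 30): Weeks 2, 4, 8, 12, 14, 16, 20, 24, 30. Patterns: 2^9 − 1 = 511.
- US visits (Part A only, SAP 3.1; last dose Week 10, follow-up 8 weeks later, so Week 18): Weeks 2, 4, 8, 12, 18. Patterns: 2^5 − 1 = 31.
- Nominal weeks, no missing samples, baseline negative unless stated.

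**Non-US schedule**

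1. *P1 with T2 (12 versus 16 weeks).* This needs a spacing of at least 12 and less than 16 weeks, with Week 30 negative. The first/last pairs are 2/14, 2/16, 4/16, 8/20 and 12/24. Visits in between may take either value: 2^3 + 2^4 + 2^3 + 2^3 + 2^3 = 48.
2. *P3 with T1 or T2.* The last positive must be Week 20 (30 − 20 = 10) or Week 24 (30 − 24 = 6), with Week 30 negative. Single positives give 2. For T2, the last positive at Week 20 allows a first positive at 8, 12, 14 or 16: 8 + 4 + 2 + 1 = 15. The last positive at Week 24 allows 12, 14, 16 or 20: again 15. Total 2 + 15 + 15 = 32, of which 16 (pairs 8/20 and 12/24) are already in step 1.
3. *P2 with T1.* Positive at Week 30 only: 1.
4. Both: 48 + 32 − 16 + 1 = **65 of 511**. Persistent only 415, transient only 31, neither 0 (415 + 65 + 31 = 511).

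**US schedule.** The longest spacing before Week 18 is 12 − 2 = 10 weeks, so the 12/16-week mismatch contributes nothing. P3 with T1 or T2 gives 12 and P2 with T1 gives 1: **13 of 31** both, 15 persistent only, 3 transient only. Part B starters with a Week 12 baseline have the same visit spacing (Weeks 14, 16, 20, 24, 30), so they also give 13 of 31.

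**Worked patients**

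| Positive at | Negative at Week 30? | Persistent by | Transient by |
|---|---|---|---|
| Weeks 8, 20 | yes | P1, P3 | T2 |
| Weeks 4, 16 | yes | P1 | T2 |
| Week 24 only | yes | P3 | T1 |
| Week 30 only | no | P2 | T1 |

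**Does one cut-off suffice?**

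| Rule | Non-US, both | US, both |
|---|---|---|
| As written | 65 | 13 |
| P1 and T2 both at 12 weeks | 17 | 13 |
| P1 and T2 both at 16 weeks, P3 left at 12 | 33 | 13 |
| Transient = positive and not persistent | 0 | 0 |

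Under the last rule, with the persistent clauses as they stand, the split is 415 + 65 = 480 persistent and 31 transient (US: 28 and 3).

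**Baseline-positive patients.** P2 and T1 require a negative baseline; P1, P3 and T2 do not. On the non-US schedule 62 of 511 patterns are both and 10 are neither. SAP 8.7.1 expects such patients, since it restricts one assay to them.

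**The case against.** - *The consequence is limited.* This stands. ADA summaries are descriptive, no other analysis in the SAP uses the persistent/transient split, and derived data will be listed (SAP 8.1), so cases could be reclassified. Primary and key secondary inference is untouched.
- *65 of 511 is not an expected effect.* This also stands. It weights implausible alternating sequences equally with plausible ones, and the documents give no ADA incidence. It shows that the rules overlap, not how many patients are affected.
- *The secondary objective names the three Part A regimens, so naming Arms 1–3 is reasonable.* That could justify separate columns for those arms. It does not reconcile 8.7.1 with an analysis set that is defined without regard to arm and assigned to all immunogenicity analyses.
- *A reader might infer that Part B starters are left out of the ADA evaluation, and that about a third of exposed patients would be missing.* The documents do not support this. Only one sentence reads that way; SAP 6.1.4, 7.1 and 8.7 and Protocol 11.6 all include these patients. The fraction would come from 40 placebo participants plus an assumed 20–50% of 40 adalimumab participants, giving 48–60 of 168–180 (29–33%). It assumes that everyone enters Part B, whereas US participants have Part A only, so it is an upper bound on the number for whom the SAP is ambiguous.

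**Conclusion.** The overlap is wrong as written: 8.7.1 places some patients in both categories and gives no rule to decide. It arises from three separate clashes (P1 with T2, P3 with T1 or T2, P2 with T1), only the first of which comes from the differing cut-offs. It affects particular patterns, not every ADA-positive patient, and the number affected cannot be estimated from the documents.

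The arm sentence is an internal inconsistency, not an established omission.

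The counts assume nominal visit weeks, complete sampling and literal reading of the clauses. Four of the five first/last pairs in the mismatch are exactly 12 weeks apart nominally, so on actual dates, with visit windows of ±2 days, an individual patient could fall on either side of the persistent limit. The SAP should be corrected before the ADA tables are produced; no efficacy conclusion depends on it.

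**What to change.** 1. Choose one cut-off for all the spacing clauses, and state whether spacing is measured on nominal visits or actual dates.
2. Restrict both terms to treatment-emergent ADA-positive patients as 8.7.1 already defines them. Without this, a baseline-positive patient with no titre boost who is positive at Weeks 2 and 16 counts as persistent but not treatment-emergent, and the categories cannot sum to that total.
3. Define persistent first. Define transient as treatment-emergent positive and not persistent. The two are then exclusive and sum to the treatment-emergent total.
4. Decide explicitly whether a single positive shortly before a negative last visit, or only at the last visit, belongs under persistent; step 3 places it there if P2 and P3 are kept.
5. Replace the Arms 1–3 sentence so that the tables cover every sonelokimab-exposed participant in the immunogenicity set, including Arm 4 participants and Arm 5 non-responders who start sonelokimab in Part B. Use the existing baseline at first sonelokimab dose, and show these participants separately if that is clearer.

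Cost: SAP wording and table programming. The samples are already scheduled for all participants.

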### 8.7.2 Pharmacokinetic Analyses

Blood samples will be collected for the measurement of trough serum sonelokimab levels at Baseline, Week 2, Week 4, Week 8, Week 12, Week 14, Week 16, Week 20 and Week 24. At dosing visits the samples will be collected prior to dose administration.

Serum concentrations of sonelokimab will be summarized by visit including number of observations, number of concentrations below the quantifiable limit (nBLQ), mean, SD, GM, CV, median, min and max. All concentration values reported as no results (not collected or ND) will be treated as missing. For the calculation of concentration summaries, all concentrations below the quantifiable limit (BLQ) will be set to the BLQ value/2.

The PK measurements for sonelokimab will be listed by-participant, by visit and by treatment group. Individual values of concentrations and PK parameters will be presented with 3 significant digits.

Two plots of the PK concentrations will be presented for Part A:

1. A plot of the individual PK concentration profiles with study week on the x-axis and concentration on the y-axis, with log10 spacing on the y-axis. One page will be used for each Sonelokimab arm, with the individual concentration profiles overlaid for each dose.
2. A single plot of the geometric mean concentration profiles for each Sonelokimab arm with study week on the x-axis and concentration on the y-axis, with log10 spacing on the y-axis.

Additional analyses may be performed at the sponsor's discretion, but they are beyond the scope of this SAP and will be specified in a separate document, if needed.

## 8.9 Safety Analyses

For all the safety endpoints, no formal statistical testing will be performed. Safety summaries will be presented by treatment group separately for the Part A (SAF), Part B (SAF-Part B), and Part A+B (SAF).

For Part A, 6 groups will be considered:

- Sonelokimab 120 mg (Q2W),
- Sonelokimab 60 mg (Q2W),
- Sonelokimab 60 mg (Q4W),
- Placebo,
- Adalimumab 40 mg (Q2W),
- Total sonelokimab.

For Part B and follow-up period, 10 groups will be considered:

- Sonelokimab 120 mg Q2W→sonelokimab 120 mg Q4W;
- Sonelokimab 120 mg Q2W→adalimumab 40 mg Q2W;
- Sonelokimab 60 mg Q2W→sonelokimab 60 mg Q4W;
- Sonelokimab 60 mg Q2W→sonelokimab 120 mg Q4W;
- Sonelokimab 60 mg Q4W→sonelokimab 60 mg Q4W;
- Sonelokimab 60 mg Q4W→sonelokimab 120 mg Q4W;
- Placebo→sonelokimab 120 mg Q4W;

- Adalimumab 40 mg Q2W→adalimumab 40 mg Q2W;
- Adalimumab 40 mg Q2W→sonelokimab 120 mg Q2W.
- Total sonelokimab

For Part A+B, 5 groups will be considered:

- Placebo (Part A only)
- Total Sonelokimab 120mg
- Total Sonelokimab 60mg
- Total Sonelokimab
- Total Adalimumab 40mg Q2W

The placebo group will include all subjects who were randomized to placebo in Part A and will only include Part A summary visits.

The total Sonelokimab 120mg group will include all subjects who were randomized to Sonelokimab 120mg Q2W in Part A and subjects who had Sonelokimab 120mg Q2W or Q4W in Part B. Subjects will only be included for summary visits during the Part they were assigned 120mg Q2W.

The total Sonelokimab 60mg group will include all subjects who were randomized to Sonelokimab 60mg Q2W or Q4W in Part A and subjects who had Sonelokimab 60mg during part B (Sonelokimab 60mg Q2W responders and Sonelokimab 60mg Q4W responders). Subjects will only be included for summary visits during the Part they were assigned Sonelokimab 60mg.

The total Adalimumab 40mg Q2W group will include all subjects who were randomized to Adalimumab 40mg Q2W during Part A and subjects who had Adalimumab 40mg Q2W during part B (Adalimumab 40mg Q2W responders and Sonelokimab 120mg Q2W non-responders).

The total Sonelokimab arm will include subjects who received sonelokimab at any time in the study. Subjects will only be included for summary visits during the Part they were assigned Sonelokimab.

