#### Number of Participants:

Approximately 200 participants will be assigned to randomized treatment, for a planned number of approximately 40 participants in each of the 5 treatment arms (with a randomization ratio of 1:1:1:1:1). The total number of participants with previous use of biologic agents will be capped at 30%.

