### 3.3.1 Sonelokimab

Sonelokimab drug product is supplied as a fixed-dose, prefilled syringe to be administered via subcutaneous (SC) injection. Syringes and cartons will be supplied in a blinded manner.

Sonelokimab will be administered by a site-approved, study treatment administrator, who is unblinded. Blinded study personnel will not be in attendance while study treatment is being prepared or administered.

In Part A, the 3 sonelokimab treatment arms are as follows:

- Arm 1 (sonelokimab 120 mg Q2W): Sonelokimab 120 mg will be given as SC injection at Weeks 0, 2, 4, 6 and 8. Participants will receive a placebo injection at Week 10 to maintain the blind;
- Arm 2 (sonelokimab 60 mg Q2W): Sonelokimab 60 mg will be given as SC injection at Weeks 0, 2, 4, 6 and 8. Participants will receive a placebo injection at Week 10 to maintain the blind;
- Arm 3 (sonelokimab 60 mg Q4W): Sonelokimab 60 mg will be given as SC injection at Weeks 0, 4 and 8. Participants will receive a placebo injection at Weeks 2, 6 and 10 to maintain the blind.

In Part B, after allocation of responders and non-responders, the sonelokimab treatment arms are as follows:

- Responders from Arm 1, non-responders from Arm 2, non-responders from Arm 3, and participants from Arm 4 will receive sonelokimab 120 mg Q4W until Week 20. Placebo injections will be given at Weeks 14, 18, and 22 to maintain the blind;
- Responders from Arm 2 and responders from Arm 3 will receive sonelokimab 60 mg Q4W until Week 20. Placebo injections will be given at Weeks 14, 18, and 22 to maintain the blind;

- Non-responders in Arm 5 will receive sonelokimab 120 mg Q2W with SC injections at Weeks 12, 14, 16, 18, and 20. Participants will receive a placebo injection at Week 22 to maintain the blind.

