- Sonelokimab 120 mg Q2W→sonelokimab 120 mg Q4W;
- Sonelokimab 120 mg Q2W→adalimumab 40 mg Q2W;
- Sonelokimab 60 mg Q2W→sonelokimab 60 mg Q4W;
- Sonelokimab 60 mg Q2W→sonelokimab 120 mg Q4W;
- Sonelokimab 60 mg Q4W→sonelokimab 60 mg Q4W;
- Sonelokimab 60 mg Q4W→sonelokimab 120 mg Q4W;
- Placebo→sonelokimab 120 mg Q4W;
- Adalimumab 40 mg Q2W→adalimumab 40 mg Q2W;
- Adalimumab 40 mg Q2W→sonelokimab 120 mg Q2W.
- Total sonelokimab (safety tables only)

**Part A+B:** For Part A+B no statistical testing will be performed. Summary statistics will be based on the data collected from the visit Week 0 to Week 24. Part A+B tables will only be presented for adverse events.

Unless otherwise stated, the summary statistics will be presented for the following treatment groups:

- Placebo (Part A only)
- Total Sonelokimab 120mg
- Total Sonelokimab 60mg
- Total Adalimumab 40mg Q2W
- Total Sonelokimab

For the total groups they will have different subjects potentially for Part A and Part B and subjects will only have results shown for the Part when they took the relevant treatment.

All participant data, including those derived, will be presented in individual participant data listings. Unless otherwise stated, unscheduled visit results will be included in date/time chronological order, within participant listings only. All listings will be sorted by treatment group, investigational site, participant number, date/time, and visit. The treatment group as well as participant's sex, age and race will be stated on each listing. Unless otherwise stated, safety data listings will be based on SAF and efficacy data listings will be based on FAS.

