## 8.9.1 Adverse Events

All AEs will be classified by Primary SOC and PT according to MedDRA Version 25.0 or higher and will be graded according to the National Cancer Institute Common Terminology Criteria for Adverse Events (NCI CTCAE) version 5.0.

AEs will be summarized by SOC and PT using counts and percentage (i.e., number and percentage of participants with an AE). AEs will be sorted by decreasing frequency within each SOC and PT as per the overall column.

Where a participant has the same AE, based on PT reported multiple times, the participant will only be counted once at that PT level. Where a participant has multiple AEs within the same SOC, the participant will only be counted once at that SOC level.

If a participant experiences the same AE more than once with different severity grades, then the event with the highest severity will be tabulated by maximum severity. In addition, AEs with a missing severity will be presented in the summary table under the category of ‘Missing’ and will not be imputed.

TEAEs are defined as any AE occurring or worsening on or after the first dose of study treatment.

TEAEs will be assigned to Part A, Part B and Part A+B using the event start date and time and will be defined as:

- Part A: events started on or after the first dose of study medication for Part A but not after Part B or events present prior to the first dose of study medication for Part A but increased in severity on or after dosing on Part A but not after Part B
- Part B: events started on or after the first dose of study medication for Part B or events present prior to the first dose of study medication for Part B but increased in severity on or after dosing on Part B

For Part A+B treatment emergent AEs relating to the Part when the subject was on the corresponding treatment are considered as TEAE.

Adverse events with an onset on Day 1 which are based upon pre-dose lab tests will be considered as not treatment emergent. These are defined as:

- Adverse events which begin on study day 1 with SOC = “Investigations” or PT in (“Hypercholesterolaemia” “Hyperlipidaemia” “Dyslipidaemia”, “Type V hyperlipidaemia”).
- The latest lab test taken on Day 1 has a time which is before the treatment start time.

Treatment-related AEs are those events with relationship to study drug ‘Related’ as recorded on the CRF. If the relationship to study drug is missing, the AE will be considered as treatment related.

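### SAP 8.9 admits 120 mg Q4W dosing in Part B to the pooled Part A+B 120 mg safety group, then limits inclusion to Parts assigned 120 mg Q2W, which read literally removes all Q4W data from that adverse event column

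*Combined protocol and SAP*

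**What the plan says.** SAP 8.9 lists five groups for the Part A+B safety summaries. Total Sonelokimab 120mg takes everyone randomized to 120 mg Q2W in Part A, plus "subjects who had Sonelokimab 120mg Q2W or Q4W in Part B". The sentence that follows sets the periods that count: "Subjects will only be included for summary visits during the Part they were assigned 120mg Q2W". Q4W is not named there.

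Three nearby rules are worded differently:

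- The matching sentence for the 60 mg group restricts by dose alone: "Subjects will only be included for summary visits during the Part they were assigned Sonelokimab 60mg".
- SAP 8.1, on the total groups, says "subjects will only have results shown for the Part when they took the relevant treatment".
- SAP 8.9.1 gives the attribution rule: "For Part A+B treatment emergent AEs relating to the Part when the subject was on the corresponding treatment are considered as TEAE".

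SAP 3.3.1 states who receives 120 mg in Part B. For Q4W: "Responders from Arm 1, non-responders from Arm 2, non-responders from Arm 3, and participants from Arm 4 will receive sonelokimab 120 mg Q4W". For Q2W: "Non-responders in Arm 5 will receive sonelokimab 120 mg Q2W".

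**The concern.** The two adjacent sentences cannot both be followed. The first admits Part B participants on 120 mg Q4W, and the second leaves them no Part B period to contribute. Arm 1 responders would be counted for Part A only. Arm 2 and Arm 3 non-responders and all placebo participants would belong to the group with no countable period.

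This column pools adverse events by dose across both Parts. A programmer who follows the restriction would produce a 120 mg column made up of Arm 1 in Part A plus Arm 5 non-responders in Part B, under a label that promises all 120 mg exposure. If participant counts or exposure time were taken from the broader definition while events were taken from the narrower one, percentages and exposure-adjusted rates for the higher dose would come out too low.

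**Working it through.** The plan gives no size for this group, so there is no figure of its own to reproduce. The effect can be counted from the allocation table.

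**Inputs**

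- About 40 participants per arm (protocol synopsis, Number of Participants).
- Part B allocation by Week 12 response (SAP Table 1 and 3.3.1).
- Week 12 responder proportions r1, r2, r3 and r5 for Arms 1, 2, 3 and 5. The documents give no rates for the 20% joint-count criterion, so these are assumptions, scanned from 40% to 80%. The nearest figure is an ACR20 response of roughly 50% to 60% on TNF inhibitors (protocol 6.1.1).
- No dropout, and every participant enters Part B.

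**By sequence**

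| Part A | Part B treatment with 120 mg | Kept by the literal rule in Part B? |
|---|---|---|
| Arm 1 responders | 120 mg Q4W | No |
| Arm 2 non-responders | 120 mg Q4W | No |
| Arm 3 non-responders | 120 mg Q4W | No |
| Arm 4, all | 120 mg Q4W | No |
| Arm 5 non-responders | 120 mg Q2W | Yes |

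Four of the five are removed.

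**By participants**

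- 120 mg Q4W in Part B: Q4 = 40 × [r1 + (1 − r2) + (1 − r3) + 1]
- 120 mg Q2W in Part B: Q2 = 40 × (1 − r5)
- Share of Part B 120 mg participants removed: Q4 / (Q4 + Q2)
- Share of pooled participant-Parts removed (one participant in one Part, with 40 from Arm 1 in Part A): Q4 / (40 + Q4 + Q2)

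| Assumed rates | Q4 | Q2 | Part B share removed | Pooled share removed |
|---|---|---|---|---|
| r1 = r2 = r3 = 0.60, r5 = 0.55 | 96 | 18 | 96/114 = 84% | 96/154 = 62% |
| Lowest in scan: r1 = 0.4, r2 = r3 = 0.8, r5 = 0.4 | 72 | 24 | 72/96 = 75% | 72/136 = 53% |
| Highest in scan: r1 = 0.8, r2 = r3 = 0.4, r5 = 0.8 | 120 | 8 | 120/128 = 94% | 120/168 = 71% |

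At the arithmetical floor (r1 = 0, r2 = r3 = 1, r5 = 0) the rule still removes 40 of 80 Part B participants, because all of Arm 4 goes to 120 mg Q4W whatever the response.

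**US participants.** They have no Part B (SAP 3.1). With an assumed 20% US share in every arm and the rates in the first row, Q4 = 76.8 and Q2 = 14.4. The Part B share stays at 76.8/91.2 = 84%, and the pooled share falls to 76.8/131.2 = 59%.

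**Participant denominator.** In the first-row case the membership sentence gives 40 (Arm 1) + 16 + 16 (Arm 2 and 3 non-responders) + 40 (placebo) + 18 (Arm 5 non-responders) = 130 people. Of these, 16 + 16 + 40 = 72 (55%) have no countable Part under the restriction. Using 130 as the denominator with events from the restricted periods would dilute every percentage.

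**Exposure-adjusted rate.** SAP 8.9.1 calls for these rates for Part A+B. Appendix K estimates the rate as D/T, participants with at least one event over total time. It runs time to the last Part B visit or study discontinuation for those randomized to sonelokimab. For those randomized to placebo or adalimumab, sonelokimab time starts at the first Part B dose. If Q4W events leave D while Q4W time stays in T, the 120 mg rate falls. The direction is clear. The size cannot be computed, because the documents give no event rates and Appendix K does not say how time is split by dose.

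**The case against.** The strongest reply is that this is one stray frequency in an otherwise consistent plan. The membership sentence, the 60 mg sentence, SAP 8.1 and SAP 8.9.1 all go by dose or by the relevant treatment, and SAP 8.5 presents Part A+B exposure for sonelokimab 120 mg without a frequency. A careful programmer would infer the intent. That shows which sentence is the outlier, and it is probably a drafting slip. It does not cancel an explicit inclusion rule. SAP section 9 does not address the conflict, and protocol 12.3.4 lists only the nine sequences for Part B and the whole period, so it offers no rule for a pooled dose group.

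The reply is right about reach, and three stronger readings should be resisted.

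- A reader might infer that most Part B 120 mg safety data disappear from the report. They do not. SAP 8.9 tabulates all four Q4W sequences in the Part B tables, including placebo to 120 mg Q4W, and they remain in Total Sonelokimab. Laboratory, vital sign and ECG summaries are made separately for Part A and Part B, so they do not use this column.
- A reader might take the column to be the main safety summary by dose. Nothing in the documents ranks it so. The safety objective compares the three regimens with placebo, which exists only in Part A, and those tables are unaffected.
- A reader might expect the 120 mg and 60 mg participant counts to sum to Total Sonelokimab once corrected. They would not, because Arm 2 and Arm 3 non-responders take both doses and are counted once in the total.

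**Conclusion.** Wrong as written: an internal inconsistency in an analysis rule. Followed literally, the restriction removes all Part B 120 mg Q4W data, 4 of the 5 Part B sequences containing 120 mg, from the pooled Part A+B 120 mg adverse event column. The 75% to 94% and 53% to 71% ranges rest on 40 per arm, no dropout, full entry to Part B, and assumed response rates varying independently from 40% to 80%. They illustrate scale and do not forecast the actual counts. The sequence count needs no response assumption. The downward bias in the exposure-adjusted rate is conditional: it arises only if events and time are restricted differently. Nothing here touches the Part A comparisons, the by-sequence Part B tables, Total Sonelokimab or any efficacy analysis.

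**What to change.** Reconcile the two sentences in SAP 8.9. Replace the restriction for the 120 mg group with wording by dose, for example: *during the Part(s) they were assigned sonelokimab 120 mg (Q2W or Q4W)*. This matches the 60 mg sentence and agrees with SAP 8.1 and 8.9.1.

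Also state that the same treatment periods define events, participant denominators and exposure time in each pooled group, and align Appendix K with that by saying how time is divided when a participant changes dose or drug at Week 12.

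The cost is one changed SAP sentence, a short clarification in Appendix K, and one treatment-period flag in the analysis datasets. Treatment, data collection and efficacy analyses do not change. It should be settled before the Part A+B tables are programmed.
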